### **3.5 Mitigation of risks**

Potential risks of adverse reactions, renal toxicity, bone toxicity, reproductive toxicity, exacerbation of hepatitis B infection, and drug resistance are described above. These risks will be minimized as follows. Individuals will be followed closely during the trial for development of clinical or laboratory abnormalities. Individuals with baseline renal dysfunction will be excluded, and renal function will be closely monitored, using estimate creatinine clearance, during the trial. The risk of bone toxicity will be minimized by the short duration of follow-up on drug: 4 months. Women who are pregnant, lactating or desiring pregnancy in the next 4 months will be excluded. Women of reproductive capacity must agree to use an effective form of contraception during the study to minimize the risk of pregnancy. Individuals with evidence of chronic hepatitis B (HBsAg-positive) will be excluded. The potential for development of drug resistance in volunteers who become HIV-infected during the trial will be minimized by frequent HIV testing and immediate cessation of investigational product if HIV infection is diagnosed. Very few HIV infections are expected given the small sample size and short follow-up period. If the annual HIV incidence is at most 5%, we could expect <1 incident HIV infection among 72 volunteers enrolled.

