## **5.0 STUDY ENDPOINTS AND STUDY DESIGN**

### **5.1 Study Endpoints**

#### **5.1.1 Primary Endpoints**

##### *Safety and tolerability:*

- The proportion of volunteers with moderate and greater severity clinical adverse events
- The proportion of volunteers with mild, moderate and greater severity of renal toxicities, and other moderate and severe laboratory abnormalities
- The proportion of volunteers with serious adverse events

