## 12.0 **DISCONTINUATION OF ADMINISTRATION OF INVESTIGATIONAL PRODUCT AND/OR WITHDRAWAL FROM STUDY**

### 12.1 **Discontinuation of administration of investigational product**

Any volunteer discontinuing from investigational product or being considered for discontinuation of investigational product will be discussed with the sponsor. Volunteers will be discontinued from investigational product for any of the following reasons:

1. Pregnancy
2. Intercurrent HIV infection
3. A disease or condition or an adverse event that may develop, regardless of relationship to the investigational product, if the principal investigator or designee is of the opinion that further investigational product is not in the best interest of the volunteer.
4. Use of antiretroviral medications or other medications that may interact with investigational product
5. Volunteer request to discontinue further participation.
6. Participating in another clinical study of an investigational product
7. Creatinine clearance (CrCl)  $\leq 50$  mL/min, as calculated by Cockcroft-Gault formula
8. Any of the other following abnormal laboratory parameters that occur after randomization:

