**Serum Creatinine Elevation**

All Grades

Continue study medication for up to 3 days while values are confirmed

Confirmed Grade 1

Continue study medication at the discretion of the study physician  
Monitor weekly until return to within 0.3 mg/dL of the baseline value

Confirmed Grade 2-4

Permanently discontinue study drug  
Monitor as clinically indicated (generally at least monthly up to 3 months) until return to within 0.3 mg/dL of the baseline value

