### **13.3 Data Analysis**

The data analysis plan will be developed and agreed upon by the sponsor, the principal investigators and Study Chair prior to unblinding of the study. The statistician at the Data Coordinating Centre, in collaboration with the Principal Investigators and the Sponsor, will create tables according to this data analysis plan.

The DCC will conduct the data analysis and will provide interim and final study reports for the sponsor, principal investigator, the SRB and the regulatory authorities as appropriate. Senior statisticians at the collaborating research centre may participate in data analysis.

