#### **14.2.1 Safety and tolerability**

Adverse events will be classified according to the MedDRA body system and preferred terms. The number and percentage of subjects experiencing a given AE will be tabulated by treatment group, grade (severity/ relationship), and time since randomization.

Safety and tolerability will be assessed by examining the overall rates of adverse events and serious adverse events that are possibly, probably, or definitely associated with FTC/TDF. With 24 volunteers assigned to daily or intermittent FTC/TDF, observing no drug-related serious toxicity would result in an exact, two-sided, 95% confidence interval of (0.0000, 0.1425). If one drug-related SAE is observed, the exact, two-sided, 95% confidence interval would be (0.0011, 0.2112).

This study will have limited power to rule out all but very large relative increases in the risk of an adverse event due to FTC/TDF. For example, if 5% of the volunteers in the combined control group are expected to experience a given AE, this study has only 55% power to rule out a 10-fold increase (i.e., 5% vs. 50%) if there is no real increase. It has 63% power to rule-out a 15-fold increase (5% vs. 75%). For known FTC/TDF toxicities in HIV-infected persons, the observed AE rate among FTC/TDF recipients will be compared to historical data.

All clinical and routine laboratory data will be included in the safety analysis. Rate of study discontinuation and reasons for discontinuation will be determined by treatment group.

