#### **17.1.1 Content of Interim Review**

The SRB will be asked to review the following data:

- A blinded listing of all severe clinical adverse events, independent of relationship to the Investigational Product, and
- A blinded listing of all severe laboratory adverse events confirmed on retest, independent of relationship to the Investigational Product, and
- A blinded listing of all Serious Adverse Events, independent of relationship to the Investigational Product.

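### The listings for the one scheduled safety board review use a severe cut-off, so they need not show product stops that section 12.1 requires for moderate creatinine rises or low creatinine clearance

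*Protocol*

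**What the plan says.** Section 17.1 schedules one SRB review, once about a quarter of volunteers have two months of follow-up. Section 17.1.1 lists what the board will be asked to look at: severe clinical adverse events, "A blinded listing of all severe laboratory adverse events confirmed on retest", and all SAEs.

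Section 12.1 sets the product stops. Under serum creatinine elevation, the entry "Confirmed Grade 2-4" carries permanent discontinuation. Separately, reason 7 is a CrCl of 50 mL/min or less, "as calculated by Cockcroft-Gault formula". For every other laboratory value, Grade 1 or 2 leaves dosing to the study physician, and required action begins only at Grade 3.

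Appendix B grades creatinine of 1.4 to 1.8 x ULN as Grade 2 (moderate) and 1.9 to 3.4 x ULN as Grade 3 (severe). It has no row for CrCl, and its general instructions restrict the estimating category to clinical symptoms.

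The protocol gives renal toxicity special weight. The primary safety endpoints in 5.1.1 include "The proportion of volunteers with mild, moderate and greater severity of renal toxicities, and other moderate and severe laboratory abnormalities", and section 3.5 states that "renal function will be closely monitored, using estimate creatinine clearance, during the trial".

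**The concern.** The SRB listings apply one severity threshold to all laboratory events. For most values that fits section 12.1, because required action also starts at Grade 3. Creatinine and CrCl are the exceptions: the protocol considers lower levels sufficient to end dosing, yet does not require the board to see those cases.

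Only one review is scheduled. Its listings could contain no renal entry although volunteers had already been taken off product under the protocol's own renal rules. The board would then be judging whether the trial should continue without a required view of early stops for the laboratory toxicity that the protocol watches most closely. What is at stake is oversight of the trial as a whole, not the handling of any one volunteer.

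**Working it through.** The protocol states no figure on this point, so the check sets the rules side by side and then asks whether the CrCl case can really occur. I read severe as Grade 3 or higher.

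**Step 1: creatinine.**
- Product stops permanently from confirmed Grade 2, i.e. from 1.4 x ULN (12.1 and Appendix B).
- The laboratory listing starts at severe, i.e. from 1.9 x ULN (17.1.1 and Appendix B).
- A confirmed value of 1.4 to 1.8 x ULN therefore ends dosing but does not enter the laboratory listing on its grade. This step needs no outside assumption.

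**Step 2: CrCl.**
- Product stops at 50 mL/min or less, whatever the creatinine grade.
- With no CrCl row in Appendix B, the table never makes such a stop severe. It reaches the laboratory listing on grade only if creatinine itself is Grade 3 or higher.

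To see whether CrCl can reach 50 with creatinine below Grade 3, rearrange the Cockcroft-Gault formula in 5.2.4: creatinine = (140 - age) x weight x (0.85 if female) / (72 x CrCl). At CrCl 50 the denominator is 3,600. The protocol gives no ULN for creatinine; I assume 0.9 to 1.2 mg/dL for women and 1.1 to 1.4 mg/dL for men.

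| Volunteer | Creatinine at CrCl 50 | Multiple of ULN | Grade |
|---|---|---|---|
| Woman, 49 y, 45 kg | 91 x 45 x 0.85 / 3,600 = 0.97 mg/dL | 0.81 to 1.07 | at most borderline Grade 1 |
| Man, 40 y, 65 kg | 100 x 65 / 3,600 = 1.81 mg/dL | 1.29 to 1.64 | 1 to 2 |
| Man, 30 y, 90 kg | 110 x 90 / 3,600 = 2.75 mg/dL | 1.96 to 2.50 | 3 |

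So a CrCl stop below Grade 3 creatinine is a realistic case, mainly at lower body weight. In heavier volunteers creatinine can reach Grade 3 before CrCl falls to 50. These examples show that the case can arise, not how often. The two gaps also overlap, because some volunteers at CrCl 50 already have Grade 2 creatinine.

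**Step 3: the other two listings.** A renal stop appears there if it is also an SAE or a severe clinical event. Nothing makes a Grade 2 creatinine or a CrCl of 50 either of these.

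**Step 4: the requested review.** Section 17.1.2 provides a review of all safety data, but the trigger it states is two or more volunteers with SAEs definitely or probably related to product. Moderate renal stops would not by themselves bring it about.

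**Step 5: scale at the scheduled review.** 25% of 72 is 18 volunteers. Under 2:2:1:1 allocation about 18 x 4/6 = 12 of them would be on FTC/TDF. Chemistry is drawn at Weeks 4, 8 and 16 (Appendix A1), so results from the first two draws would generally exist for these volunteers.

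**The case against.** The strongest reply is that nothing here is contradictory. A stopping rule for one person and a listing for a board serve different purposes and may use different thresholds. A cautious individual rule does not oblige the board to see every case, and the endpoint definition in 5.1.1 does not govern interim listings. That is right: this is a design choice that can be improved, not an inconsistency.

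The second reply is that the board has other sources. Section 12.1 says "Any volunteer discontinuing from investigational product or being considered for discontinuation of investigational product will be discussed with the sponsor". Section 13.3 says that the data coordinating centre "will provide interim and final study reports for the sponsor, principal investigator, the SRB", among others, as appropriate. Under 17.1 the SRB oversees study progress and may invite investigators and the sponsor to an open session. Severity is finally the investigator's call (10.2), with Appendix B a guideline (9.1.1), so a low CrCl could be rated severe. All of this stands, and 17.1.1 does not exclude further data. A reader might infer that the board will not learn of renal stops; the documents do not support that, because the content of the interim reports is not stated. They support only that no route requires disclosure.

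The third reply is that the consequence is small. Entry requires CrCl of at least 60 (5.2.4), time on drug is four months (3.5), and the tubular dysfunction case reports in 3.3.1 began 5 to 16 months after starting TDF. The listings are blinded, and an extra renal line would trigger no stated rule. This also stands, and it sets the severity.

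**Conclusion.** The point holds as a low-severity improvement. As written, the required listings for the only scheduled SRB review need not show stops for confirmed Grade 2 creatinine, or for CrCl of 50 mL/min or less with creatinine below Grade 3, unless the event is also an SAE or is otherwise rated severe. The creatinine half rests on the text alone. The CrCl half rests on the absence of an Appendix B grade; the assumed ULNs only illustrate that the case can occur.

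Two stronger readings should be resisted. One is that most renal stops would be missed: without a ULN or any distribution of renal function at stopping, that share cannot be determined. The other is that volunteers are left exposed: 12.1 stops them regardless of what the board sees. Few such stops are expected, although in a trial of this size even one or two would be useful for the board to know about.

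**What to change.** In section 17.1.1, add one blinded listing that shows all product discontinuations under 12.1 with the reason, together with all confirmed creatinine values of Grade 2 or higher and all CrCl values of 50 mL/min or less.

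No new data are needed. Creatinine and CrCl are already on the schedule, and section 14.2.1 already states that "Rate of study discontinuation and reasons for discontinuation will be determined by treatment group"; for the SRB the same information would be listed blinded. The cost is one extra listing and a slightly longer SRB packet.

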#### **17.1.2 Indications for discontinuation of administration of investigational product in all Volunteers**

If 2 or more of the volunteers participating in this study develop an SAE judged definitely or probably related to the investigational product, the Principal Investigators or designees and the sponsor will request a review by the SRB. The study will be suspended pending a review of all safety data by the SRB. The study may be unblinded at the discretion of the SRB.

Following this review, the SRB will make a recommendation to the Sponsor and the Principal Investigators regarding the continuation of the study.

### **17.2 Study Supervision**

The investigator and the IAVI Medical Monitor will be provided progress report(s) of this study. Close cooperation between members of the study team will be necessary to track study progress, respond to queries about proper study implementation and management, address issues in a timely manner, and assure consistent documentation, and effective information sharing. Rates of accrual, retention, and other parameters relevant to the research centre's performance will be regularly and closely monitored by the study team.

### **17.3 Study Monitoring**

Monitoring will be conducted to ensure that the study is conducted in compliance with human subjects and other research regulations and guidelines, recorded and reported in accordance with the protocol, is consistent with locally-accepted HIV counselling practices, standard operating procedures, Good Clinical Practice (GCP) and applicable regulatory requirements.

The monitor will confirm the quality and accuracy of data at the research centre by validation CRFs against the source documents such as clinical records and against the database when applicable. The Investigators and volunteers, by giving consent, agree that the monitor may inspect study facilities and source records (e.g., informed consent forms, clinic and laboratory records, other source documents), as well as observe the performance of study procedures. Such information will be treated as strictly confidential and will under no circumstances be made publicly available.

The monitoring will adhere to Good Clinical Practice guidelines. The Principal Investigator will permit inspection of the facilities and all study-related documentation by authorized representatives of IAVI, and Government and Regulatory Authorities relevant to this study.

#### **17.4 Investigator's Records**

Study records include administrative documentation—including reports and correspondence relating to the study—as well as documentation related to each volunteer screened for and/or enrolled in the study—including informed consent forms, case report forms, and all other source documents. The investigator will maintain and store, in a secure manner, complete, accurate, and current study records for a minimum of 2 years after marketing application approval or the study is discontinued and applicable national and local health authorities are notified or the product development is discontinued. IAVI will notify the Principal Investigator of these events.

#### **18.0 INDEMNITY**

The Sponsor and collaborating research centre are responsible to have appropriate liability insurance. For research-related injuries and/or medical problems determined to result from receiving the investigational product, treatment including necessary emergency treatment and proper follow-up care will be made available to the volunteer free of charge at the expense of the Sponsor.

#### **19.0 PUBLICATION**

A primary manuscript describing safety and immune responses in this trial will be prepared promptly after the data analysis is available, based on the data compiled by the IAVI statistical centre. Authors will be representatives of each trial research centre, the statistical centre, the laboratories and IAVI, subject to the generally accepted criteria of contributions to the design, work, analysis and writing of the study. Precedence will be given to authors from the research centre enrolling the greatest number of volunteers. Manuscripts will be reviewed by representatives of each participating group as specified in the clinical trial agreement (CTA).

#### **20.0 ETHICAL CONSIDERATIONS**

The Principal Investigator will ensure that the study is conducted in compliance with the protocol, Standard Operating Procedures in accordance with guidelines laid down by the International Conference on Harmonisation for Good Clinical Practice in clinical studies, the ethical principles that have their origins in the Declaration of Helsinki and applicable regulatory requirements.

In addition to IEC/IRB and regulatory approvals, all other required approvals will be obtained before recruitment of volunteers.

## APPENDIX A1: SCHEDULE OF PROCEDURES

|                                                                                                                                                                                                                                                      | Screen | Rando |     |     |       |            |        |       |           |       | Final visit | HIV f/u 1 | HIV f/u 2 |
|------------------------------------------------------------------------------------------------------------------------------------------------------------------------------------------------------------------------------------------------------|--------|-------|-----|-----|-------|------------|--------|-------|-----------|-------|-------------|-----------|-----------|
| Study Week                                                                                                                                                                                                                                           |        | 0     | W1  | W2  | W4    | W4+ 24 hrs | W8     | W12   | W16 or ET | W24   |             |           |           |
| Visit Windows (Days)                                                                                                                                                                                                                                 |        | -42   | ± 1 | ± 2 | -7/+2 |            | - 7/+2 | -7/+2 | - 7/+2    | -7/+7 |             |           |           |
| Investigational Product                                                                                                                                                                                                                              |        |       |     |     |       |            |        |       |           |       |             |           |           |
| FTC/TDF/Placebo provision                                                                                                                                                                                                                            |        | X     |     |     | X     |            | X      | X     |           |       |             |           |           |
| Drug accountability (pill count/unused pills)                                                                                                                                                                                                        |        |       |     |     | X     |            | X      | X     | X         |       |             |           |           |
| Upload MEMS data                                                                                                                                                                                                                                     |        |       |     |     | X     |            | X      | X     | X         |       |             |           |           |
| Consent / Counselling / Assessments / Questionnaires                                                                                                                                                                                                 |        |       |     |     |       |            |        |       |           |       |             |           |           |
| Informed Consent and assessment of understanding                                                                                                                                                                                                     | X      |       |     |     |       |            |        |       |           |       |             |           |           |
| Screening Questionnaire                                                                                                                                                                                                                              | X      |       |     |     |       |            |        |       |           |       |             |           |           |
| HIV risk Assessment                                                                                                                                                                                                                                  |        | X     |     |     |       |            |        |       |           |       |             |           |           |
| Pre-/Post HIV-test counselling                                                                                                                                                                                                                       | X      | X     |     |     | X     |            | X      | X     | X         | X     | X**         | X**       |           |
| HIV risk reduction counselling / Family planning counselling                                                                                                                                                                                         | X      | X     |     |     | X     |            | X      | X     |           | X***  | X           | X         |           |
| Adherence counselling                                                                                                                                                                                                                                |        | X     | X   | X   | X     |            | X      | X     |           |       |             |           |           |
| Follow-back interview (adherence, sexual risk behaviour, medication sharing)                                                                                                                                                                         |        |       | X   | X   | X     |            | X      | X     | X         |       |             |           |           |
| Acceptability assessment (focus group/individual interview)                                                                                                                                                                                          |        |       |     |     |       |            |        |       | X*        |       |             |           |           |
| IVR or SMS behavioural assessment                                                                                                                                                                                                                    |        | Daily |     |     |       |            |        |       |           |       |             |           |           |
| Clinical Safety Assessments                                                                                                                                                                                                                          |        |       |     |     |       |            |        |       |           |       |             |           |           |
| Medical History including Concomitant Medications                                                                                                                                                                                                    | X      | X     | X   | X   | X     |            | X      | X     | X         |       | X           | X         |           |
| General Physical Exam****                                                                                                                                                                                                                            | X      |       |     |     |       |            |        |       | X         |       | X           |           |           |
| Directed Physical Exam *****                                                                                                                                                                                                                         |        | X     | X   | X   | X     |            | X      | X     |           |       |             | X         |           |
| Adverse Events/ Serious Adverse Events                                                                                                                                                                                                               |        | X     | X   | X   | X     |            | X      | X     | X         |       |             |           |           |
| Lab Samples                                                                                                                                                                                                                                          |        |       |     |     |       |            |        |       |           |       |             |           |           |
| Hep BsAg and STI screening: urine for gonorrhoea and chlamydia; blood for syphilis; additionally for females vaginal swab for trichomonas, Candida vaginitis & bacterial vaginosis .
+ Swab to collect mucosal secretions for antibody secretion. | X      |       |     |     |       |            |        |       |           |       |             |           |           |
| Haematology (CBC) (+ plasma storage)                                                                                                                                                                                                                 | X      |       |     |     | X     |            | X      |       | X         |       | X           |           |           |
| Clinical Chemistry (creatinine, creatinine clearance, pancreatic amylase † , serum phosphate, aspartate transferase (AST), alanine transferase (ALT), total bilirubin                                                                     | X      |       |     |     | X     |            | X      |       | X         |       | X           |           |           |
| Urine dipstick +/- urinalysis                                                                                                                                                                                                                        | X      |       |     |     |       |            |        |       |           |       |             |           |           |
| HIV test                                                                                                                                                                                                                                             | X      | X     |     |     | X     |            | X      | X     | X         | X     | X**         | X**       |           |
| Pregnancy Test (all female volunteers)                                                                                                                                                                                                               | X      | X     |     |     | X     |            | X      | X     | X         |       |             |           |           |
| Hair samples for adherence assessment                                                                                                                                                                                                                |        |       |     |     |       |            | X      |       | X         |       |             |           |           |
| Drug plasma and intracellular level testing                                                                                                                                                                                                          |        |       |     |     | X††   | X          | X      | X     | X         | X     | X           | X         |           |
| PBMCs (antibodies and cellular response against HIV antigens, intracellular drug levels, serum and plasma storage)                                                                                                                                   |        | X     |     |     | X     |            | X      | X     | X         | X     | X           | X         |           |
| Sample for HLA typing and related testing                                                                                                                                                                                                            |        | X     |     |     |       |            |        |       |           |       |             |           |           |
| CD4+ count, HIV viral load, p24 antigen, HIV genotyping, viral tropism assay, HIV sequencing                                                                                                                                                         |        |       |     |     |       |            |        |       |           |       | X           |           |           |

ET = Early Termination

HIV f/u 1 and HIV f/u 2 = Additional visits for HIV infected individuals after discontinuing investigational product to characterize infection and assess for the development of drug resistance mutations.

†Screening visit only

††Blood specimens for plasma and intracellular drug levels collected before and approx. 2 hours after witnessed administration of investigational product as part of the single-dose, timed pharmacokinetic study at Week 4 visit

\*Focus group/individual interview will take place as soon as possible after the final study visit.

\*\*If needed to confirm HIV diagnosis

\*\*\* Only HIV risk reduction counseling

\*\*\*\* A general physical examination includes the following: weight, height (at screening visit only), vital signs, and examination of skin, respiratory, cardio-vascular, central nervous and abdominal systems, external ano-genitalia (screening only) and an assessment of cervical and axillary lymph nodes

\*\*\*\*\* Symptom directed physical examination including vital signs (pulse, respiratory rate, blood pressure and temperature), and any further examination indicated by history or observation

